| **Background and rationale for the study** | Multiple sclerosis (MS) is the first cause of progressive neurological disability in young adults.  In the relapsing-remitting (RR) form of the disease, the pathophysiology is dominated by the inflammatory response, and a range of effective immune-modulating therapies have been successfully developed. In progressive MS (PMS), different pathophysiologic mechanisms seem to interact, resulting in myelin damage and neurodegeneration through incompletely understood events. Therefore, while targeting inflammatory pathways has advanced the efficacy of treatments in RRMS, progressive forms lag behind^1^. Furthermore, progression of disability develops in MS independently of disease phase: disability can accrue insidiously also during the RR phase of the disease^2,3^. Furthermore, a significant percentage of people with RRMS, even though treated with the most effective therapies, still develop secondary progressive MS (SPMS)^4^.  Osmotin is a protein initially characterized as associated with stress adaptation in plant cells^5^. Actinidia Deliciosa plants overexpressing the osmotin protein were developed at the University of Tuscia in Italy, and tested for ten years for their improved agronomic and nutritional qualities^6^. In addition, it has been shown in different plant species that the overexpression of the osmotin plant gene increases the production of flavon-3-ols and other anti-inflammatory plant compounds ^30^. In mammals, osmotin binds the adiponectin receptor due to the 3D structure homology between the two proteins^7^. As such, it may share some of the anti-inflammatory effects of adiponectin^8-10, 28^. Indeed, this appears to be the case with the attenuation of LPS-induced neuroinflammation^11^ and with preventive effects on vascular inflammation in atherosclerosis^10^. Osmotin also protects against glutamate-induced synaptic dysfunction and neurodegeneration in the rat brain, and attenuates LPS-induced neuroinflammation^11^. However, adiponectin also has pro-inflammatory functions^12^. High and low molecular weight isoforms of the adiponectin molecule may play different roles in inflammation^13,14^. This may explain conflicting results on the role of adiponectin in MS^15-25^. However, because osmotin and adiponectin have different amino acid sequences, with the exception of the active site ^29^, osmotin may not manifest the negative effects that may be associated with adiponectin polymers. Additionally, the anti-inflammatory effects of Actinidia plants are well-documented ^27^.  Based on these premises, a nutraceutical product (commercial name Forza) has been developed by 9^th^ Dimension Biotech, Inc., consisting of the lyophilized leaves of the A. Deliciosa plants bioencapsulating recombinant osmotin, with the goal of offering the combined benefits of the osmotin protein in conjunction with the enhanced anti-inflammatory properties of the bioengineered A. Deliciosa plants to consumers. In fact, as recently as in 2016, it has been shown that the bioencapsulation of protein drugs in lyophilized plant cells represents an ideal method of oral protein drug delivery to patients, which surpasses all other methods of protein drug delivery both in safety and efficacy^26^. Therefore, it may be worth exploring the effects of Forza in MS, where Forza may play both anti-inflammatory and neuroprotective effects. Considering the strong need to identify therapies for the progressive forms of the disease, we here propose to explore the effects of Forza in progressive MS (PMS). Moreover, the low impact of current therapies in PMS may not overshadow possible effects of Forza, something that would probably happen with high efficacy treatments in RRMS. |
|  |  |
| **Objectives** | This study aims at verifying the safety and to explore the clinical and biological efficacy of Forza in PMS. |
|  |  |
| **Design** | Prospective, multicenter, single-arm non-interventional study. |
|  |  |
| **Patients** | Patients with a progressive form of MS will be enrolled by the MS Center of the Clinica Neurologica San Martino Hospital in Genoa and of Sant ’Andrea Hospital of Rome.  A sample of 50 patients guarantee a 90% power to detect a reduction of 20% in the Neurofilament change rate (assuming a SD=40%) during the treatment period as compared to the pre-treatment period. |
|  |  |
| **Inclusion/exclusion criteria** | patients with PMS meeting the inclusion criteria will be included in the trial. |
|  |  |
| **Methods** | Patients meeting all inclusion/exclusion criteria will be included in the study after having provided their written informed consent.  They will undergo two pre-treatment assessments: at -6 months (-6M) and at baseline visit (M0) and two post-treatment assessments at month 1 (M1), and at month 6 (M6).  The treatment will consist in the oral administration of a minimum dosage of 5 grams per day of Forza, provided in the form of capsules. Each capsule will contain approximately 0.7g of Forza. The capsules will be administered as follow: 4 capsules in the morning and 3 additional capsules in the evening from baseline () to month 6 (M6).  At each timepoint the following assessments will be evaluated: electrophysiological (motor evoked potentials – MEPs; somatosensory evoked potentials – SEPs; visual evoked potentials – VEPs), optical coherence tomography (OCT), and neurofilaments (NfL).  In addition, clinician assessed outcomes (CAO), patient reported outcomes (PRO) and performance measure (PF) will be acquired for the motor domain (Expanded Disability Status Scale – EDSS; Timed 25 Foot Walk - T25FW; 12-item Multiple Sclerosis Walking Scale - MSWS12; Nine-Hole Peg Test - 9HPT), for the cognitive domain (Montreal Cognitive Assessment - MOCA; Symbol Digit Modalities Test - SDMT), for the emotional domain (Hospital Anxiety and Depression Scale - HADS), and for the bladder domain (Overactive Bladder - OAB).  Brain MRI will also be obtained at each timepoint as standard of care procedure.  In order to investigate the potential effect of Forza on brain metabolism (concentration of glutamate, N-acetylaspartate, creatine, choline) and microstructure, a subgroup of 25 patients (enrolled at the University of Genoa) will undergo MRI with a multi-shell diffusion-weighted (DWI) sequence and proton magnetic resonance spectroscopy (1H-MRI) in addition to routine sequences. |
| **Endpoints** | The primary outcome of the study will be safety, and the co-primary efficacy outcome will be a reduction in the NfL change over 1 and 6 months as compared to the pre-treatment NfL change. |
| **Statistical analysis** | The NfL percentage changes will be compared pre and post treatment within patients by a non-parametric paired Wilcoxon test. |
| **Expected results** | We expect to verify the safety of an add-on therapy with *Forza* in PMS and to obtain clinical, paraclinical and laboratory information on the effects of *Forza* in this condition. |
|  |  |

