**Secondary objectives**

Secondary objectives of the study are:

- Exploring the clinical and biological efficacy of Forza in PMS both after one month and six months of treatment or at the end of the study (in case of early withdrawal).

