## METHODS

**Study design**

This is a prospective, multicenter, single-arm non-interventional study. It consists of a first visit six months before the assumption of osmotin (-6M), in which the investigators will inform patients about the study design and objective and the possibility to take part of it.

Then, only after having obtained a written informed consent, demographics characteristics and info about MS history will be collected, and clinical evaluations and assessments will be performed.

During a subsequent baseline visit, six months after the first one, (0M) the same clinical evaluations and assessments will be performed and after their execution the treatment will be administered and taken by the patients.

Two post treatment follow up visits are planned at 1 month (1M) and six months (6M) after the baseline, in which the same clinical evaluations and assessments will be recorded.

Patients meet all inclusion/exclusion criteria will be included in the study after having provided their written informed consent.

They will undergo two pre-treatment assessments: at -6 months (-6M) and at baseline visit (M0) and two post-treatment assessments at month 1 (M1), and at month 6 (M6).

The treatment will consist in the oral administration of Forza capsules at a minimum dosage of 5 grams per day.

At each timepoint the following assessments will be evaluated:

- Electrophysiological (motor evoked potentials – MEPs; somatosensory evoked potentials – SEPs; visual evoked potentials – VEPs)
- Optical coherence tomography (OCT)
- Neurofilaments (NfL)

In addition, clinician assessed outcomes (CAO), patient reported outcomes (PRO) and performance measure (PF) will be acquired for investigating the following domains:

- Motor domain (Expanded Disability Status Scale – EDSS; Timed 25 Foot Walk - T25FW; 12-item Multiple Sclerosis Walking Scale - MSWS12; Nine-Hole Peg Test - 9HPT)
- Cognitive domain (Montreal Cognitive Assessment - MOCA; Symbol Digit Modalities Test - SDMT)
- Emotional domain (Hospital Anxiety and Depression Scale - HADS), and for the bladder domain (Overactive Bladder - OAB).

Brain MRI will also be obtained at each timepoint as standard of care procedure.

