In order to investigate the potential effect of Forza on brain metabolism (concentration of glutamate, N-acetylaspartate, creatine, choline) and microstructure, a subgroup of 25 patients (enrolled at the University of Genoa) will undergo MRI with a multi-shell diffusion-weighted (DWI) sequence and proton magnetic resonance spectroscopy (1H-MRI) in addition to routine sequences.

Any changes on disease modifying therapy (DMT), any occurrence of adverse events during treatment period and any interruption of treatment will be recorded on the medical chart.

[figure not shown]

[figure not shown]

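### The protocol does not provide for masked reading of stored MRI, DWI/spectroscopy, OCT and evoked-potential records, although the visit date reveals treatment status and there is no control arm

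*Supplement*

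**What the plan says.** The Synopsis describes the design as "Prospective, multicenter, single-arm non-interventional study". The Methods sections of the Synopsis and of the protocol body schedule two visits before Forza (-6M, 0M) and two on it (1M, 6M).

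The wording on the measures differs by type:

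- **Evoked potentials and OCT** (with NfL): "At each timepoint the following assessments will be evaluated: electrophysiological (motor evoked potentials", continuing with the other modalities.
- **Routine MRI** (Study design): "Brain MRI will also be obtained at each timepoint as standard of care procedure".
- **DWI and spectroscopy** (Study design): "a subgroup of 25 patients (enrolled at the University of Genoa) will undergo MRI with a multi-shell diffusion-weighted (DWI) sequence", with spectroscopy added, for the stated purpose of looking for an effect of Forza on brain metabolism and microstructure.

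These measures come under the secondary objective: "Exploring the clinical and biological efficacy of Forza in PMS both after one month and six months of treatment". The Statistical analysis section compares pre- and post-treatment changes in continuous variables by paired t-test or Wilcoxon signed-rank test, with 0.05 as the significance cut-off. The co-primary efficacy outcome is a different one: "the co-primary efficacy outcome will be a reduction in the NfL change over 1 and 6 months".

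No section mentions masking, independent or central reading, who the reader is, or the order and timing of reading. The sections on data collection and statistical methods add nothing on this.

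**The concern.** EDSS, the performance tests and the questionnaires cannot be masked to visit in an open single-arm study. Stored images, spectra, OCT scans and evoked-potential traces can be. They are the clinical and paraclinical measures best placed to support biological efficacy independently of what patients and clinicians expect.

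That independence is not secured if the reader can see the date. Where deriving a measure involves judgement, a reader who expects improvement may shift the on-treatment values slightly. In a randomised trial read without knowledge of arm, such a shift would fall on both arms. Here it falls only on records made after 0M and cannot be told apart from an effect of Forza.

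**Working it through.** **1. What the text establishes and what it leaves open**

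| Element | Wording in the protocol | Reader, timing and masking of the reading |
|---|---|---|
| Evoked potentials, OCT | evaluated at each timepoint | not stated |
| Routine MRI | obtained at each timepoint | not stated |
| DWI, spectroscopy (n=25) | patients undergo the scan | not stated |

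Visits and treatment periods coincide for every patient (-6M and 0M off Forza, 1M and 6M on), so an undisguised date or visit label gives the treatment status. The flow chart also limits which records exist: MEPs have no mark at +1 month, and SEPs and VEPs have no row, although the Methods text lists them for every timepoint.

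**2. The plan's own figure**

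The Estimated sample size section gives 50 patients, 90% power, a 20% reduction and SD 40% for NfL. Taking 40% as the SD of the within-patient difference, the standardised effect is 20/40 = 0.5.

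- Normal approximation: n = ((1.960 + 1.282)/0.5)² = 42.0, so 43.
- Paired t-test: n = 44; power at 50 is 93.4%.
- Wilcoxon with worst-case efficiency 0.864: 43.995/0.864 = 50.9, so 51.

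The stated 50 is therefore reproduced to within one patient under the last allowance. It rests on NfL alone, so masked reading of the other measures leaves it unchanged.

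**3. How a reading bias enters the paired difference**

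Suppose reading shifts every on-treatment value by b, in SD units of the paired difference. The change from -6M to 0M is unaffected, the change from 0M to 6M moves by b, and so their difference moves by b.

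A steady drift of d per month behaves differently. It adds 6d to each of those two six-month changes, and 6d − 6d = 0.

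The choice of contrast matters. If the post-treatment change were taken from 1M to 6M, as in the sample-size statement, a constant on-treatment shift would cancel (b − b = 0), but steady drift would leave 5d − 6d = −d. The Statistical analysis section does not fix the contrast for these measures. For MEPs, with no mark at 1M, the change from 0M to 6M is the only one available.

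**4. Illustrative size**

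The documents give no value for b, so the values below are assumptions. With no true effect, the paired t statistic has noncentrality b√n. The two-sided 5% rejection probability, from the noncentral t distribution, is:

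| Assumed b | b√25 | n = 25 | b√50 | n = 50 |
|---|---|---|---|---|
| 0 | 0 | 5% | 0 | 5% |
| 0.1 | 0.5 | 8% | 0.71 | 11% |
| 0.2 | 1.0 | 16% | 1.41 | 28% |
| 0.3 | 1.5 | 30% | 2.12 | 55% |
| 0.4 | 2.0 | 48% | 2.83 | 79% |

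n=25 is the DWI/spectroscopy subgroup, and n=50 is a measure available in all patients. The figures apply to each measure tested. The protocol does not state whether tests are two-sided; two-sided is assumed.

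**The case against.** A reader might infer that the plan has all these biomarkers read unmasked, visit by visit, by people who know which recordings are on Forza. The text does not say so. The verb *evaluated* covers evoked potentials, OCT and NfL only; MRI is *obtained*, and patients *undergo* the extra scans. Even for evoked potentials and OCT the phrase is schedule language, and the Study design section elsewhere speaks of the same assessments being performed and recorded. Knowledge of treatment status is thus possible under the plan, not prescribed by it.

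Further points stand:

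- The protocol does not say whether the measures are derived by hand or by software. With automated derivation the bias may be small.
- A reader might also infer that masked reading would remove the bias. It cannot undo what happens at acquisition, such as voxel placement at the scanner or recording of evoked potentials by staff who know the treatment status. Time trend, regression to the mean and changes in disease-modifying therapy also remain.
- Steady drift in reading practice cancels if equal six-month changes are compared, so drift is not automatically tied to the treated period.
- The measures are exploratory, and no decision rule rests on them.
- The size of b has no source in the documents.

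These points narrow the claim but do not dispose of it. The protocol allows reading with knowledge of treatment status, the measures can produce p-values for an efficacy objective, and the safeguard is available.

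**Conclusion.** The point holds as an omission: masked reading of stored records is not provided for in a single-arm study where the date reveals treatment status. It does not hold as a statement that readers are unmasked.

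Its reach is limited to exploratory imaging, OCT and electrophysiological measures. Safety, NfL and the sample size of 50 are unaffected. The size cannot be derived from the documents. The range of 8% to 48% per measure at n=25 follows entirely from assuming a bias of 0.1 to 0.4 SD of the paired difference, a two-sided paired t-test, and a contrast that sets on-treatment records against untreated ones. It shows that a modest bias could matter, not that one is present. This is a worthwhile, inexpensive improvement rather than a fault in the main analysis.

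**What to change.** In Methods (Synopsis) and Study design, separate acquisition from derivation:

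- Acquire and quality-check every record at its scheduled visit, so that unusable scans or spectra are found in time.
- Derive the study measures after the patient's last visit from stored records, with date and visit removed, in random order within patient, by the same existing reader for all of that patient's records.
- Keep the routine clinical MRI report at the time of the scan and separate from the study measurement.
- Say in the report that this protects the reading step only.

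EDSS, performance tests and questionnaires stay as planned.

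The cost is file coding at two centres, later availability of the study values, and possibly a second marking of evoked potentials already marked at recording. No extra patients, visits, acquisitions or staff are needed, and no planned decision depends on biomarker values during follow-up.

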## STUDY OBJECTIVES

**Primary objective**

The study aims to address the following primary objective:

- Verify the safety of Forza in PMS during the entire treatment period.

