**Statistical analysis**

All collected data will be analyzed using descriptive statistics. Continuous variables will be described with number of patients with valid observations, mean, standard deviation, median, minimum and maximum value. If necessary, additional descriptive statistics may be calculated (in particular, for non-normally distributed data, the median with interquartile range). Categorical data will be described by frequencies and related percentages within variable. A p-value of 0.05 will be used as the cut off for statistical significance (no statistical test will be used for safety data).

Any comparisons between pre- and post- changes in continuous variables will be evaluated with paired sample t-test or Wilcoxon signed rank-test, as appropriate.

In particular, all safety and efficacy data will be analyzed using descriptive statistics. Safety data will be assessed by reporting and describing all the adverse events. Decisions following the safety pattern will be discussed by the study investigators, but no logic based on statistical test was set.

Depending on the results of interest, a stratified or an exploratory analysis may be conducted.

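### NfL is co-primary in the synopsis but secondary in the objectives, and nothing says which NfL contrast decides or whether one or both months must succeed

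*Supplement*

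**What the plan says.** The Endpoints row of the synopsis reads: "The primary outcome of the study will be safety, and the co-primary efficacy outcome will be a reduction in the NfL change over 1 and" (the sentence then adds month 6 and sets both against the pre-treatment change). The synopsis row on statistical analysis adds that NfL percentage changes will be "compared pre and post treatment within patients by a non-parametric paired Wilcoxon test".

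The body of the protocol ranks things differently. The sole primary objective is: "Verify the safety of Forza in PMS during the entire treatment period". The secondary objective is: "Exploring the clinical and biological efficacy of Forza in PMS both after one month and six months of treatment", or at study end for early withdrawals. NfL is not named there.

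The Estimated sample size paragraph gives 50 patients, 90% power, a 20% reduction in the NfL change rate and an SD of 40%. It compares 6M-1M with the period from -6M to 0M.

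The Statistical analysis section says that "all safety and efficacy data will be analyzed using descriptive statistics". It also says "A p-value of 0.05 will be used as the cut off for statistical significance", excludes tests for safety data only, and allows a paired t-test or Wilcoxon signed-rank test for pre-post comparisons of continuous variables. It gives no testing order, no adjustment and no designated time point.

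**The concern.** NfL is the only efficacy outcome on which the study is sized, so its rank decides how a significant result may be described. On the synopsis, p<0.05 would be a co-primary success. On the objectives, the same p-value would be an exploratory observation. Either description could cite the protocol after the data are seen.

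Within the synopsis, the co-primary outcome covers two time points with no rule for combining them. A claim resting on either month has a false-positive rate above 5%; a claim needing both does not. The powered contrast (6M-1M) matches neither the 1-month nor the 6-month change, so the sample-size justification is not tied to the endpoint it should support. With a single arm there is no concurrent comparison to act as a check, which makes a fixed endpoint and rule matter more.

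**Working it through.** **Inputs from the protocol.** N = 50, power 90%, effect 20%, SD 40% (Estimated sample size); cut-off 0.05, no test for safety (Statistical analysis); visits at -6M, 0M, 1M and 6M. **Assumptions, because the protocol is silent:** tests are two-sided, and the SD of 40% is that of the paired difference, so the standardised effect is 20/40 = 0.5.

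**1. The plan's own figure.** n = ((z0.975 + z0.90) × SD/δ)² = ((1.960 + 1.282) × 40/20)² ≈ 42.0, so 43 patients (44 by the t distribution). With N = 50, power is Φ(0.5 × √50 − 1.960) = Φ(1.576) = 94.2%. The noncentral t gives 93.4%, and a simulated paired Wilcoxon test (normal data, 20,000 runs) gives 92.3%. Fifty patients therefore deliver at least the stated 90% for one contrast at 0.05.

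The result depends on what the SD describes. If 40% is the SD within each period and the two periods are uncorrelated, the SD of the difference is 40 × √2 = 56.6. The standardised effect is then 20/56.6 = 0.354, power at N = 50 is about 69%, and 87 patients are needed.

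**2. How the NfL contrasts relate.** Write y for NfL at each visit, with independent errors of equal variance (taken as 1) and simple differences:
- D1 = (y1 − y0) − (y0 − y−6) = y1 − 2y0 + y−6, variance 1 + 4 + 1 = 6
- D6 = y6 − 2y0 + y−6, variance 6
- Covariance of D1 and D6 = 4 + 1 = 5, so correlation = 5/6 ≈ 0.83

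**3. Chance of at least one false positive, two tests each at two-sided 0.05** (bivariate normal):

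| Case | Either direction | Benefit only |
|---|---|---|
| Nominal, one test | 5% | 2.5% |
| Correlation 0.9 | 7.0% | 3.5% |
| Correlation 5/6 | 7.6% | 3.8% |
| Independent (upper limit) | 1 − 0.95² = 9.75% | 1 − 0.975² = 4.94% |

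Simulated Wilcoxon tests at N = 50 give 7.8% for the 5/6 case.

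If changes are expressed per month, D1 becomes y1 − (7/6)y0 + (1/6)y−6. Its correlation with D6 is 15/√(86 × 6) = 0.66, and the either-direction figure is about 8.5%, still under the limit.

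**4. If both months are required.** Under the same assumptions, the chance that both are significant under the null is 5% + 5% − 7.6% = 2.4%. There is no inflation. The unstated rule alone moves the error rate of the NfL claim from about 2.4% to about 7.6%.

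**5. The powered window.** 6M-1M spans five months, leaves out the first month of treatment, and is set against a six-month pre-treatment period. It is neither of the changes named in the synopsis.

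**The case against.** This is a 50-patient, single-arm study whose objectives speak of exploring efficacy, and no separate analysis plan is shown. Multiplicity details are commonly left to such a plan. That is fair for the adjustment method. It does not cover rank: the protocol states it twice, differently, and a later plan would have to overrule one of the protocol's own statements.

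It is also fair that the synopsis does not say either month suffices, and that the inflation is moderate even if it does. Safety is untested and uses no share of the 0.05.

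A reader might infer more than the text supports:
- **A third rank, descriptive only.** The Statistical analysis section does not say only. It also plans paired tests and sets a cut-off, and description is a method rather than a rank.
- **A clash over the test.** The synopsis names Wilcoxon for NfL specifically; the body gives a general rule for continuous variables. Reading the specific statement as governing NfL reconciles them.
- **Three chances at significance.** Counting 6M-1M as a third test gives about 10.6%, but that window appears only in the sample-size paragraph, and nothing says three windows will each be tested.
- **Insufficient power once alpha is split.** At 0.025 per month, power is 90.2% by the normal formula, 88.5% by t and 87.1% by Wilcoxon. This is a small shortfall at most, under a split that the plan does not state and that is not needed here.

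**Conclusion.** The conflict of rank is plain on the text: NfL is co-primary in the synopsis, while the objectives give safety alone as primary and efficacy as secondary and exploratory. The decisive NfL contrast and the rule across the two months are not defined, and the powered window is a different one again. This is wrong as written, not just short of detail.

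The statistical cost is conditional and moderate. If either month may carry the claim, the two-sided error rate is about 7.6% (limit 9.75%), or about 3.8% against 2.5% for false claims of benefit. This rests on independent, equal-variance visit errors. If both months must succeed, nothing is inflated. It would go too far to say that the plan grants two chances at significance: it fails to exclude that reading. Nor is the sample size shown to be wrong, provided the SD of 40% belongs to the paired difference.

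**What to change.** Give NfL one rank in the synopsis Endpoints row and in the primary and secondary objectives.

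If it stays co-primary:
- Name one confirmatory contrast: the change from 0M to 6M against the change from -6M to 0M. Both periods are six months long.
- Test it two-sided at 0.05 by the paired Wilcoxon test that the synopsis already names.
- Bring the sample-size window (now 6M-1M) into line with that contrast, and state whether the SD of 40% is that of the paired difference.
- Make the 1-month result and all other outcomes supportive, reported as estimates with 95% confidence intervals.
- Say in the Statistical analysis section that this NfL test is the confirmatory exception to the descriptive analysis.

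If NfL is secondary, remove co-primary from the synopsis and report NfL as exploratory.

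The cost is a few sentences, with no added patients or visits. The single test holds the error rate at 5% and keeps about 92-93% power at N = 50 if the SD is that of the paired difference (about 69% if it is per period and uncorrelated). The downside is that the 1-month result can no longer carry the efficacy claim alone.
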